### **Health Economic Examinations after 2 and 4 year follow ups**

1. Data from NPR and KUHR/KPR:

Date of treatment, diagnosis and procedure codes (ICD-10 and NCSP)

Type and length of treatment (day, full day or outpatient)

Costs (DRG-code, DRG-weight and corrected DRG-weight)

Level of care (hospital, GP, GP acute and emergent)

Reimbursement code and information regarding patient payment (HELFO)

In the qualitative part of this study an individual semi-structured interview will be conducted of a choice of guardians from both follow-up groups from up-to 3 timepoints; within the first 14 days, 6 and 24 months after drain insertion. The interview guide will at each timepoint have neutral and open questions about themes that contain the guardians' expectations and experiences related to the operation or follow up after drain operation. Themes which spontaneously come up under the interview will be explored further.

All interviews are planned to be completed by the same researcher with a length not normally exceeding 60 minutes. Interviews will be performed with the help of recording and transcribed verbatim. Interviews will be performed such that personal information is protected. The original interviews are planned to be completed in person at the institution near the patient for example their associated hospital or by home visit. The Covid-19 pandemic required the use of telephones for these interviews.

### **Statistical analysis**

Linear mixed model (LMM) with center as random factor will be used to examine if there is a significant long-term effect (at 2 and 4 years) of treatment (insertion of drain) on hearing level and other audiological and clinical factors. Interaction joints will be included in the statistical model to examine the effect of treatment, measured in the form of change compared to pre-operative measurements, is the difference between patients who receive

follow-up through their GP or hospital. Log transformation of data will be actual if it is relevant to study relative over absolute changes, and transformation of data will be actual if a response variable appears to be skewed. Alternative non-parametric models can be used as needed.

Differences between the two randomization groups (hospital, GP) taking into account severity of complications, number of reoperations and proportion of re-referrals under the follow up period will be examined with the help of chi-squared tests (as a categorical variable) or Mann-Whitney test of differences of the entirety. It will also be actual to compare groups taking into account re-operation rate, and identify riskfactors for recurrence (re-operation), by using different types of survival analysis models, alternatively a logistic regression (if one can not account for time for re-operation).

If there is no significant difference between groups, we will focus on magnitude of differences between groups. With a lack of significant difference we will use a 95% confidence interval for absolute difference around 0 (around 1 for relative difference), but border values in the interval must be less than that which is considered a clinical difference of significance. What these values are will depend on which factors are being analyzed.

The health economic analyses will be performed based on randomization and where follow up has been performed.

In the qualitative portion of the study the transcription of interviews will be done continuously. Multiple researchers belonging to the research group and the project will collaborate to read and analyze the transcript. The analysis method will be adjusted to the data and presented problems.

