### **Project Description:**

## **The ConVenTu-study (Control of Ventilation Tubes)**

**- A randomized, controlled multicenter study -**

### **Background**

Ventilation tubes (drains) in the ear drum are one of the most common operations on children both in Norway and internationally (1,2). This intervention is performed to better hearing and speech development and to reduce ear complaints (3). Long term results of drain treatment are under discussion (4,5). A Cochrane report from 2010 concluded that drains had a positive effect on hearing in children with secretory otitis, but that effect was reduced after six to nine months (6). A systematic review of children with recurrent otitis concluded that drain insertion reduced the incidence of acute otitis with only one episode in the first six months after operation (7). Despite this, when this operation is performed follow up is planned to make sure that the drains are functioning, hearing is bettered, and potential complications are properly diagnosed and treated (8). Examples of complications are running ears, blocked tubes, early or lack of drain extrusion, persistent perforation of the ear drum or cholesteatoma (9).

According to national guidelines children are to be controlled until the middle ear is air filled and normalized, or the best possible result is attained, which can take several years. The first control is recommended after one month and thereafter every 4th month (10) while other countries have made follow up less comprehensive (11). A Scottish study found that few controls resulted in interventions and recommended that children be controlled after 3 months and thereafter only as needed (12). Swedens SBU (Statens beredning for medicinsk utvärdering) wrote in 2008 that there is no documented assessments of how and when a child who has had implanted drains should be followed up (13).

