### **Goals**

The overall goal of the study was to find out if controls after drain implantation in the ear drum can be performed as needed by the GP without it having negative consequences for the patient. We also wish to examine if differing follow up after the drain implantation in the ear drum effects the long term effects of the operation.

The primary endpoints are the childrens' hearing two and four years after the operation and secondary endpoints are fluid in the middle ear, number of re-operations, subjective complaints, complication rate and patient satisfaction. Our nullhypothesis is that there is no difference in hearing and other effect variables, and the alternative hypothesis is that there is a difference.

The qualitative part of this study has, as a goal, to collect new information from parents/guardians to children between the ages of 3-10 years who receive implanted middle ear ventilation tubes. The goal is to gather knowledge about guardians expectations with drain treatment and follow-up. Semi-structured interviews of guardians from both follow-up groups will provide new and important information from users of health care services and contribute to overall knowledge base.

We wish to also undergo a health-economic analysis to calculate the course of the patients' treatment/follow up for patients in both the specialist and primary health care systems using data from the Norwegian patient register (NPR) and Control and payment of health refunds (KUHR) now Municipal patient and user register (KPR). This will provide insight into costs for differing levels of healthcare and knowledge about quality of life adjusted life years as a consequence of this intervention.

The results of this study are expected to be published in at least 3 articles which will form part of a PhD degree.

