## **Design and procedure**

Randomized multicenter study where the primary goal is childrens change in hearing. Other audiological data, number of reoperations, subjective problems, complication rate and patient satisfaction will also be examined. We will follow the CONSORT rules. Questions regarding enrollment in the study as well as consent occur at the outpatient clinic prior to operation for children who are planned in to operation. Inclusion and randomization occur immediately after the child's operation. This, to prevent the inclusion of patients who would later be stricken from the operating list. Data collected from those who are not operated on will be shredded.

Children will be randomized to follow up after operation to either the hospital or to the GP. Follow-up through the hospital involves a control every 6 months as long as there is a clinical need for it. GP controls will only be performed as required. Guardians will be given written information as to when drain controls are recommended through their GPs; for example with ear secretion, persistent reduced hearing, ear infection, etc. GPs will receive a procedure for controls and how one should tackle the most common complications. This procedure will be attached to the discharge report from drain insertion so that it will be available for the GP under the consultation.

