## **Inclusion Criteria**

Children 3-10 years of age who receive an implanted drain through St. Olavs Hospital, Molde Hospital, Ålesund Hospital, Kristiansund Hospital, Gjøvik Hospital Innlandet and Stavanger Universityhospital. The lower age bracket is set to allow for hearing tests of children. The upper age bracket is set as children older than 10 years of age at initial operation often have additional illnesses which would prevent them from being candidates in this study.

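### The protocol plans to test a long-term effect of drain insertion, but every child has a drain and only follow-up is randomised, so for 4-year and secondary outcomes that effect cannot be identified

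*Combined protocol and SAP*

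**What the plan says.** The opening sentence of the protocol's Statistical analysis section gives the linear mixed model, with centre as random factor, the task to "examine if there is a significant long-term effect (at 2 and 4 years) of treatment (insertion of drain) on hearing level" and on other audiological and clinical factors. The parenthesis defines treatment as the drain, not the follow-up. The next sentence adds interaction terms to compare GP and hospital patients on the effect of treatment, "measured in the form of change compared to pre-operative measurements".

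The design is set out elsewhere in the protocol:

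- Inclusion Criteria: "Children 3-10 years of age who receive an implanted drain".
- Design and procedure, on timing: "Inclusion and randomization occur immediately after the child's operation".
- Design and procedure, on what is allocated: "Children will be randomized to follow up after operation to either the hospital or to the GP".
- Design and procedure, on children who leave the operating list: "Data collected from those who are not operated on will be shredded".

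The Background calls the long-term results of drain treatment unsettled. It cites a Cochrane review which found a benefit for hearing, but "that effect was reduced after six to nine months".

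The SAP (sections 5.4.1, 8.1.1 and 8.1.2) confines the primary analysis to GP versus specialist follow-up at 2 years and states no test of a drain effect. For key secondary outcomes it promises summary statistics only. It gives no 4-year analysis.

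**The concern.** A test of a treatment effect needs a group without the treatment, or some other way of knowing what would have happened without it. This trial has neither. No arm goes without a drain or has it delayed, data on children not operated on are destroyed, and neither document describes an external control, a natural-history adjustment or a caution about causal reading. The only quantity the model can offer as an effect of the drain is the change from before to after the operation.

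That change mixes at least four things: any effect of the drain, spontaneous recovery of the middle ear, 2 to 4 years of growing older and better at hearing tests, and regression to the mean in children selected for surgery. An age covariate would not separate them, because all children have the same operation at time zero and none provides untreated follow-up. Two and four years are also where attribution is hardest on the protocol's own account, since it reports that the benefit for hearing had already faded within the first year.

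At stake is a significant time term being read as a long-term benefit of drains, a question that the protocol treats as open.

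**Working it through.** **1. What the planned sample size supports.** Inputs from the protocol, Number of participants: difference between groups 5 dB, SD 10 dB, two-sided 5%. Per group, n = 2(z₀.₉₇₅ + z_power)² × SD² / difference².

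- 90% power: 2 × (1.960 + 1.282)² × 100/25 ≈ 84.1, so 85.
- 95% power: 2 × (1.960 + 1.645)² × 100/25 ≈ 104.0; the t-based calculation gives 104.9.

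The stated 85 (105) is reproduced. It concerns the difference between follow-up groups, not a drain effect.

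**2. A before-after test with no drain effect.** Inputs:

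- N = 270, from 135 per group (SAP 5.3); N = 216 after the planned 20% drop-out (270 × 0.8); N = 400 as in the protocol's target.
- SD of change 10 dB: an assumption, taking the protocol's SD as that of the change.
- Natural mean change m, from any cause other than the drain: not in the documents, so a range is shown.

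Formulas: SE = 10/√N. Probability of significance = Φ(m/SE − 1.96) + Φ(−m/SE − 1.96).

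For N = 270, SE = 10/√270 = 0.609 dB, so a mean change of 1.96 × 0.609 = 1.19 dB is significant. At m = 2 dB the probability is Φ(2/0.609 − 1.96) = Φ(1.33) ≈ 0.91.

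| Natural change | N = 216 (SE 0.680) | N = 270 (SE 0.609) | N = 400 (SE 0.500) |
|---|---|---|---|
| 0 dB | 5% | 5% | 5% |
| 1 dB | 31% | 38% | 52% |
| 2 dB | 84% | 91% | 98% |
| 3 dB | 99% | about 100% | about 100% |
| 5 dB | about 100% | about 100% | about 100% |

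The mean change detected with 90% power is (1.960 + 1.282) × SE: 2.21, 1.97 and 1.62 dB respectively. All lie well below the 5 dB that the protocol calls the smallest clinically relevant change.

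**3. The randomised contrast under the same conditions.** A natural change shared by both arms cancels in the difference between them. A simulation (20,000 trials, 135 per arm, SD 10 dB, shared change of 0, 1, 2, 5 or 10 dB, no true difference) agrees: the between-arm t-test rejects in 4.9% to 5.3% of trials. In the same runs the before-after test rejects in 5.2%, 37.6%, 90.8%, 100% and 100%, matching the formula.

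**4. Where the sentence still governs.** The SAP replaces it for 2-year hearing. For 4-year hearing and for audiological and clinical secondary outcomes, the protocol section is the only inferential plan. Its planned comparisons of complications, re-operations and re-referrals are between the randomised groups, so they do not have this problem.

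**The case against.** The strongest reply is that a drain effect is not an aim of the study. The Goals ask whether the type of follow-up changes the outcome, and the null hypothesis and the power calculation concern differences between groups. The sentence can then be read as loosely describing the time term of a model whose purpose is the interaction. The phrase about change from pre-operative values does stand in the interaction sentence. The SAP, the later document, tests no drain effect. Much of this stands: it limits the point to the 4-year and secondary outcomes and makes the remedy one of wording. It does not remove the point, because the protocol names the drain as the treatment and asks for a significance test of its effect. However that effect is measured, the design offers only change over time.

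A reader might infer more than the documents support:

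- *The main comparison is biased.* It is not. Recovery and ageing are common to both arms in expectation.
- *The test is almost certain to be significant whatever the drain does.* That needs a natural change of roughly 2 dB or more, which the documents do not give. At 1 dB the figure is 38%. The 5 and 10 dB improvements in the protocol are a sample-size scenario, not a forecast.
- *The result will be published as a benefit of drains.* The Goals promise at least three articles but give no topics. Misreading is a risk, not a stated plan.
- *The health-economic aim has the same flaw.* The Goals mention "quality of life adjusted life years as a consequence of this intervention", which could be taken to mean the drain. But the Statistical analysis section bases those analyses on randomisation and place of follow-up. The drain sentence does not name quality of life either.

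**Conclusion.** The planned test of a drain effect is wrong as written. The fault is non-identifiability: in a cohort where every child has a drain, its effect cannot be told apart from time. This follows from the design alone and rests on no numerical assumption. The percentages are illustrations. They assume an SD of change of 10 dB, a normal approximation and a natural change that the documents do not supply, and they show that even a shift far below clinical relevance would often be declared significant.

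The reach is limited. The SAP's 2-year primary comparison and the sample size are untouched. What remains is the inference on 4-year and secondary outcomes under the protocol's Statistical analysis section. It should be corrected because the correction is cheap and removes a conclusion that the data cannot carry.

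**What to change.** In the protocol's Statistical analysis section:

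1. Remove the test of a long-term effect of drain insertion.
2. Report change since before the operation within each arm descriptively, as a mean with 95% confidence interval at 2 and 4 years, labelled as change in children who all received drains and not attributable to the drain.
3. Confine inference to the randomised time-by-arm contrast, GP versus hospital follow-up, for hearing and for the other audiological and clinical outcomes.

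Wording that would serve: the mixed model will estimate the difference between follow-up groups in change since before the operation; change within each group is descriptive and will not be tested or interpreted as an effect of the drain.

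The cost is an edit to the text. No data, visits or participants are added, and neither the sample size nor the primary analysis changes. The downside is the loss of a causal claim about drains, which this design cannot support.

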### **Ethics**

Studies of drain insertion in children have not previously found a difference in hearing function with GP follow up when compared to hospital follow up (14, 15). Children where one expects an increased complication rate after drain insertion will be excluded from the study and will be followed at the hospital. Should complications of worsening occur the GP will refer the child back to the nearest hospital in keeping with other children who require help in the specialist health care system. In addition to this they will receive a direct number to ENT which the GP can use should they have questions regarding the participants, and they will as need be provided with a quick consultation. All participants will be controlled by an ENT doctor or audiographer before the operation, as well as after 2 and 4 years. The children who, due to registered findings, have a need for further follow up or consultation, will be offered so quickly.

There is normally no risk associated with audiometry, tympanometry or the other tests which are planned to be used in this study. This is normal treatment procedure in the examination of hearing and ear drums in the specialist health care system.

Informed consent will be collected surrounding participation in the study. Guardians must consent for themselves and by proxy for their children. In the information brochure about the study it is also stated that children have the ability to refuse and that it is possible to drop out of the study after having consented. Those that require additional information are asked to take contact by telephone. Project participants are included in the study only after having turned in written consent. Consultations related to this study are free of charge. Those who do not wish to participate will be followed up in hospital as is normal.

Indirect identifiable information from NPR and KUHR/KPR will give a significant supply of knowledge for the study, but will also be an extra burden for the participants. The attachment of treatment information was not requested in the initial REC-application and existing information and consent does not cover the attachment of such data. A new information and consent form is therefore being made which will be provided to further inclusions. An additional consent and information form will be provided to those already included in the study. For those who have completed 2 year follow up a new consent sheet will be mailed to them. Those who have not yet completed 2 year control will be asked for additional consent at the 2 year control. Refusal will not bear consequences for their access to a 2 year control as planned.

In the qualitative part of the study written information handout and consent form will be provided to the guardians before participation after their child is included in the main study. Benefits to participation in the qualitative study are that the guardians can share their own expectations and experiences from their child's treatment and follow up. This takes care of the user perspective. We do not consider the time used to interview to be a problem. Refusal will not bear consequences for participation in the main study.

## **Privacy**

Informants (children, medical data and parent answers on self report forms) will not be identifiable without the use of a special ID number. Electronic data and that which the researchers will use will only have the ID number and initials under the analysis of data. Project assistants will know the patients identity and key to the ID number while data is being collected. The key as well as the data itself will be kept in a locked area outside of the use of project assistants. Audiometric data will be saved in the child's hospital journal since this is assumed to be important information for the patients regardless of this study.

One applies for help of the department for applied clinical research, DMF, NTNU, for the use of “WebCRF” a solution with good data security. Registered data is secured also when they are deidentified and registered. PC-access is protected by username and password. The project leaders, researchers and coordinators PCs are networked.

The project is approved by the Regional committee for medical research ethics in south east B (2015/902).

In the qualitative part of the study sound files will be deleted as soon as the interviews are transcribed and controlled. The transcribed interviews will not contain identifiable data. Participants will be referred to as informant 1,2,3, etc. The ID key from the main study exists, is physical and is locked up at St Olavs Hospital. Transcribed interviews are saved electronically on access controlled file areas on St. Olavs hospital servers.

The qualitative study is previously treated as a quality assurance project (previously assessed by the REK, then as a separate project, attached to ConVenTu) and approved by St Olavs Hospital. Since the qualitative part of the study would like to include different regions and will be performed by the same people as ConVenTu and therefore wishes to be included as a completely integrated study under ConVenTu a change request has been filed. The privacy representatives believe this to be useful from a privacy perspective.

#### **ID number:**

Each patient will be coded with a number which is attached to a name and government personal ID number when the patient is included in the study and is registered in “Web-CRF”. This coding will be performed at the audiology center/out-patient clinic at each respective hospital on the specially designed form. The same ID number will be used on all information regarding the child and its parents. Personal information will be stored physically locked in the project office at each hospital as long as the study is being performed and will be shredded at most 5 years after project completion 31.12.2032. The registration of data available to the researcher is not personally identifiable.

